### Measurements

Table 2 provides an overview of the type and timing of measurements in PreFalls. Assessment visits take place at baseline (inclusion = month 0), at 4, 12 and 24 months. Falls are monitored by patients over the full study period with a daily fall calendar.

**Table 2 T2:** Study schedule

Month	0	4	12	24
Sociodemographic characteristics	X			
Weight, height	X	X	X	X
Morbidity, medication	X	X	X	X
				
Risk of Fall assessment (Timed "Up and Go" Test, Chair Rising test, Romberg-Test, Tandem and Semi-Tandem Stand)	X	X	X	X
				
EuroQol Quality of Life questionnaire	X	X	X	X
Falls Efficacy Scale (FES-I) questionnaire	X	X	X	X
PAR questionnaire for physical activity level	X	X	X	X
	XXXXXXXXXXXXXXXXXXXXX			
Fall diary				
				
Fall prevention program (intervention group only)	XXXXXXXXX			

For the full study period of 24 months participants are asked to fill in a fall diary. For each day they mark whether they fell or tripped. The monthly calendar is sent to the study coordinators during the first week of the following month in a prepaid envelope. When a fall occurs, detailed information is obtained through structured telephone interviews (see Table 3). If the diary is not received within 10 days after the end of the documented month the participant is contacted by phone. In case that during follow-up some patients stop to fill in the diary they will be phoned to ask for basic information on falls (number of falls, injuries and consequences).

**Table 3 T3:** Questions asked in the telephone interview after documentation of a fall in the diary

How often nearly fallen in the previous month?
How often fallen in the previous month?
Where did the last fall happen?
Getting up without help?
Time of fall?
Reason for falling?
Injuries?
Doctor consultation?
Which doctor consulted?
Admission to hospital?
Kind of shoes at time of fall?
Used glasses at time of fall?

At each study visit the risk of fall is assessed. In the "timed up and go test" (TUG) subjects are asked to stand up from a standard chair with a seat height of between 40 and 50 cm, walk a distance of three meters at a normal pace, turn, walk back to the chair and sit down. Measurement of time (in seconds) begins at the word "go" and ends when the subject's back touching the backrest of the chair, with a shorter time taken indicating better balance ability and mobility [38,43]. The "chair stand ups-test" measures the time it takes to complete five rapid chair rise cycles (sit to stand to sit) and is an indicator of the functional strength of the lower extremity and the dynamic balance capability [44]. The static balance measurement is taken from the "Short Physical Performance Battery" (SPPB) by Guralnik et al. and consists of three measurements (side by side position, semi-tandem, and tandem position) [36].

Fear of Falling is assessed with the German version of the Falls Efficacy Scale International (FES-I) [35], physical activity by the 7-Day Physical Active Recall (PAR) [45], and quality of life with the EuroQol [46]. Furthermore, patients are asked to rate their overall health status using the visual analogue scale (range 0-100, higher scores indicating better health). All tests and questionnaires used in the study have demonstrated good validity and reliability and are well known in this field.

### Sample size justification

Sample size calculation was performed using IcebergSim software (version: Beta 3.06, Bergel 2005-2006), which allows considering intracluster correlation, which is a serious issue in cluster-randomized trials.

Calculations are based on assumptions regarding the proportion of individuals with at least one fall during a 12-month follow up period. Since expected numbers of falls per individual was around one (3 to 16 falls per ten individuals a year [47,48]), these calculations (based on Chi-square test) were considered as a reasonable approximation for the confirmatory analysis using a negative-binomial regression model, which takes into account number of falls per individual.

Based on the trial by Spice et al. [21] we assumed an intra-cluster correlation coefficient of 0.02. Further, a cluster size of 10 was considered to be realistic. Therefore, about 40 clusters (382 individuals in all) have to be included in a balanced care allocation, to detect a clinically relevant reduction of one-year fall-risk from 33% to 20%, with 80% power at two-sided level of significance of 5%.

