### Participating patients

The target population of the study are community-dwelling persons aged 65 years and older with a high risk of falls. To be included at least one of the following criteria has to be met (see section measurements for a detailed description of the tests): fall within the last 12 months, fear for falling [35], chair-stand-ups >10 sec. [36], Timed-up-and-go-Test >10 sec. [37,38], balance impairments measured by the three balance tests of the Guralnik short physical performance battery [36] or self-reported subjective balance deficits. Persons not living independently and patients suffering from physical or mental restrictions that do not allow participation in an exercise program or the assessment of risk of falling are excluded. Each participating practice is asked to recruit 10 to 15 patients. In case of problems with recruiting the regional coordinating team supports recruitment activities.

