## Discussion

Reducing falls in the elderly remains a major challenge. Falls are common in older persons and can cause notable decreases of quality of life due to fear of falling, restricted mobility and loss of autonomy as well as large costs for health care systems [1-3,50,51]. The available evidence suggests that currently available interventions to reduce falls have limited effectiveness and should target on risk population [2,16,17]. This could be due to the interventions themselves, however, it could also be that interventions were implemented and investigated in a suboptimal setting. Most fall prevention studies were planned in specialized settings. To reduce falls on a population-based level the question of the role of the general practitioners regarding the uptake of fall prevention programs by the "at risk person" still has to be further investigated. PreFalls focuses on the first health-system contact for elderly-their general practitioner. Already in the planning phase general practitioners were an important part of the interdisciplinary study team. The long-term relationship and the frequent contacts of general practitioners with their patients allow the efficient detection of persons who might be at high risk of falling. Trained staff members in the practices can support the physicians in using simple but well validated tests to reliably assess the risk. The multimodal intervention comprising group exercise in combination with an individualized home training program has been pre-tested successfully in another setting [40,41]. Local networks with trained physiotherapists or sport scientists have been set up to implement the intervention in a manner, which is both adequate and realistic for a primary care setting. From a methodological point of view it would have been preferable to randomize individual patients instead of practices, as this eliminates the possibility that recruitment processes in intervention and control practices differ. This has not been possible due to logistical reasons. While PreFalls is adequately powered to detect a clinically significant reduction in falls it is not powered to reliably detect potentially clinically relevant reduction of injurious falls, as the incidence of such events is comparably low. However, PreFalls follows current recommendations for fall prevention studies such as documenting both the number of persons falling and the number of falls per person. Careful measurement of quality of life and fear of falling is included, also monitoring of improvement in balance, body weight bearing, as well as motor coordination especially when performing activities of daily life.

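### On the stated ICC and cluster size, 382 patients give the planning chi-square test about 76% power at a true 5% level, not 80%

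*Protocol article*

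**What the plan says.** All the inputs are in the protocol article, Sample size justification.

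- Effect, power and level: a "reduction of one-year fall-risk from 33% to 20%, with 80% power at two-sided level of significance of 5" per cent.
- Clustering: "we assumed an intra-cluster correlation coefficient of 0.02", with 10 patients per cluster taken as realistic.
- Test: a chi-square comparison of the proportions with at least one fall in 12 months, run in simulation software that can take the ICC into account. The section presents this as an approximation to the confirmatory negative binomial analysis of the number of falls.
- Result: "about 40 clusters (382 individuals in all) have to be included in a balanced care allocation".

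The Abstract gives the same 382 as the number to include. Under Participating patients, "Each participating practice is asked to recruit 10 to 15 patients". Under Statistics, the primary analysis set is limited to patients with complete primary outcome information. The Discussion concludes that "PreFalls is adequately powered to detect a clinically significant reduction in falls".

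**The concern.** The section names clustering as a serious issue and gives an ICC and a cluster size, so a reader expects the total to carry the matching design effect. It carries only about a third of it: 382 is 6% above the individually randomised requirement of 360, where the inputs call for 18%.

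What is at stake is how a non-significant result would be read. The Discussion's statement about power has no other support in the document than this calculation. If 382 gives 76%, the chance of missing the assumed effect with the planning test is about 24% instead of the stated 20%.

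**Working it through.** **Inputs** (Sample size justification): p₁ = 0.33, p₂ = 0.20, difference 0.13, mean 0.265; two-sided 5% (z = 1.96); 80% power (z = 0.8416); ICC = 0.02; m = 10; 382 patients, so 191 per arm.

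**1. Requirement without clustering** (chi-square, pooled variance under the null)

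n = [1.96·√(2·0.265·0.735) + 0.8416·√(0.33·0.67 + 0.20·0.80)]² / 0.13²
= [1.96·0.6241 + 0.8416·0.6173]² / 0.0169 = 179.7, so 180 per arm and 360 in total.
The unpooled formula gives 177 per arm, 354 in total.

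**2. Allowing for clustering**

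Design effect = 1 + (10 − 1)·0.02 = 1.18.
Total = 360 × 1.18 = 424.8, about 425 patients or 43 practices of 10. The unpooled formula gives 418.

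**3. Power at the stated size**

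Power = Φ[(0.13·√n_eff − 1.96·0.6241)/0.6173], with n_eff = patients per arm divided by the design effect.

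| Patients | m | n_eff per arm | Power |
|---|---|---|---|
| 382 | 10 | 191/1.18 = 161.9 | 75.7% |
| 382 | 9.55 (382/40) | 191/1.171 = 163.1 | 76.0% |
| 400 (40 × 10) | 10 | 200/1.18 = 169.5 | 77.6% |
| 382, clustering ignored in data and test | – | 191 | 82.3% |

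The unpooled formula at 382 gives 76.4% (m = 10). A cluster-level t-test gives about 74%.

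**4. Trying to reproduce 382**

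- Back-calculated ICC at m = 10: (382/360 − 1)/9 = 0.007 (0.009 with the unpooled formula), not 0.02.
- Continuity correction: 195 per arm, 390 × 1.18 = 460.
- One-sided 5%: 335, or 371 with continuity correction.
- Data with ICC 0.02 analysed by a chi-square test that ignores it: power = Φ[(0.13·√191 − 1.96·0.6241)/(0.6173·√1.18)] = Φ(0.855) = 80.4%. Solving this for 80% gives about 378 patients. This is the only variant that matches.

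The true level of that last test is 2·[1 − Φ(1.96/√1.18)] = 2·[1 − Φ(1.804)] = 7.1%.

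**5. Check by simulation** (beta-binomial data, ICC 0.02, 191 per arm in 20 clusters, 40,000 runs)

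| Test | Power | Type I error |
|---|---|---|
| Chi-square ignoring clustering | 81.1% | 7.0% |
| Chi-square corrected by the design effect | 76.6% | 5.0% |
| Cluster-level t-test | 74.4% | 4.9% |

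**6. Incomplete outcome data** (an assumption, as the document gives no rate)

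A 10% loss leaves 171.9 per arm. Power is 71.2% with the design effect held at 1.18. It is 72.3% if clusters shrink to 9.55 × 0.9 = 8.6, with design effect 1.152.

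**The case against.** The strongest reply is that 76% is not the power of the trial's confirmatory test, which is a negative binomial regression on fall counts. That reply stands. The document gives neither fall rates by arm nor a dispersion, so the power of that model cannot be computed.

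An illustration shows how far it could differ. Assume a common dispersion in both arms, chosen so that 33% and 20% fall at least once, a design effect of 1.18 on the log rate, and a Wald test. Power at 382 is then about 80% for a control rate of 0.40 per year (the Poisson limit), 86% at 0.5 and 96% at 1.0. These figures do not show that the trial is adequately powered: they follow from the assumed common dispersion, and an intervention that spares frequent fallers less would lower them. They do show that a shortfall in the count analysis has not been demonstrated. A reader might infer that the trial as a whole is underpowered or that the Discussion's claim is false; the document supports neither.

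Three further replies:

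- **The 7% type I error.** A reader might attach it to the trial's analysis. It belongs only to a planning test that would explain 382, and that the software used such a test is itself an inference. The model under Statistics allows for a random cluster effect.
- **Losses.** A reader might call the missing loss allowance a separate error. The Measurements section provides for telephone contact when diaries are late or stopped, missing-value imputation is deferred to the SAP, and a condensed article may leave out an attrition allowance. Losses are therefore only a caveat.
- **Size.** The gap is about 4 points, or about 2 if the stated number of practices is read as 400 patients. Forty practices recruiting 10 to 15 each would yield 400 to 600. This lowers the severity, but 382 is the stated aim, and neither 382 nor 400 reaches 80%.

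**Conclusion.** The sample size statement is wrong as written. On its own assumptions (33% v 20%, chi-square test, two-sided 5%, ICC 0.02, clusters of 10), 382 analysable patients give about 76% power and 400 about 78%; 80% needs about 425, which is 43 more than stated. The result does not depend on the choice of formula: pooled, unpooled, simulated and cluster-level versions that hold the 5% level lie between about 74% and 77% at 382.

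The conclusion is limited to the chi-square surrogate on the proportion of fallers. Severity is moderate to minor: a stated figure is incorrect and a general claim rests on it, but no step of the design or analysis depends on the correction.

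**What to change.** In the Sample size justification, replace the power statement with wording such as:

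> For the chi-square approximation on the proportion of fallers, allowing for an ICC of 0.02 and a cluster size of 10, 382 analysable patients give about 76% power at a two-sided 5% level; 80% would need about 425. Incomplete 12-month data would lower this further (to about 71–72% if, for illustration, 10% were incomplete).

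If the software's test and settings are on record, state them, so that the origin of 382 is no longer a matter of inference.

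In the Discussion, tie the claim of adequate power to the corrected figure. Say that it refers to the chi-square surrogate, and that the power of the negative binomial analysis was not calculated and may differ.

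The cost is a text change and a slightly less favourable stated power. No additional enrolment is required. The existing request of 10 to 15 patients per practice already allows 382 to be treated as a minimum.

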### Statistics

Analyses of the primary endpoint, number of falls per individual within a 12 months follow up period, will be performed on base of the full-analysis set (complete information regarding the primary outcome parameter). Within this population, all subjects are considered regardless to their actual compliance and the exercise-compliance of the responsible physiotherapists respectively (intention to treat principle). The statistical analysis of the primary endpoint will be considered at a two-sided level of significance of 5%.

For the confirmatory analysis of the primary endpoint, a negative binominal regression model [49] will be employed. This model approach takes repeated falls per subject into account and allows for further consideration of random effects as cluster (responsible physiotherapist) and region.

A detailed statistical analysis plan (SAP) will be defined in advance to the final analysis, to fix detailed statistical considerations with regard to further data analyses, multiple test issue, missing value imputation and sensitivity analyses.

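### The primary analysis set is limited to patients with complete 12-month fall data, so partial follow-up that the chosen model could use is left out

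*Protocol article*

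**What the plan says.** The primary endpoint is the number of falls per person in the first 12 months. On the population, the Statistics section of the protocol article says that its analysis "will be performed on base of the full-analysis set (complete information regarding the primary outcome parameter"). The next sentence reads "Within this population, all subjects are considered regardless to their actual compliance". It disregards the physiotherapists' compliance too, and closes with the label intention to treat. For the model, "a negative binominal regression model [49] will be employed". A later SAP is to settle "multiple test issue, missing value imputation and sensitivity analyses".

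The Measurements section describes what is recorded. Patients mark falls daily for 24 months, and "The monthly calendar is sent to the study coordinators during the first week of the following month in a prepaid envelope". A diary not received within 10 days after the month ends prompts a telephone call. For patients who give up the diary altogether, "In case that during follow-up some patients stop to fill in the diary they will be phoned", and the call covers the number of falls, injuries and consequences.

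Under Study design and randomization, practices are allocated, not patients. The people at issue are therefore the enrolled patients of randomised practices.

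**The concern.** Whether a patient's 12-month fall information is complete is known only after allocation. A set defined by that condition is a complete-case set, whatever its name. The intention-to-treat label covers non-adherence to exercise and does not cover loss of outcome data.

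The excluded patients may differ from those kept. The target population is 65 or older and at high risk of falls, so death, withdrawal and loss of contact may go with fall risk. The arms also make different demands: a 16-week programme with weekly sessions in one, usual care in the other. Stopping could therefore differ by arm in frequency or in its relation to risk.

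The exclusion is not forced by the data or the model. Monthly diaries show how long each patient was observed, and negative binomial regression takes log observed time as an offset.

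Nor is this a detail left open for the SAP. The article defers imputation and sensitivity analyses but states the primary population itself. Imputing incomplete counts in the primary analysis would require that population to be redefined, and sensitivity analyses would leave the primary result on complete cases.

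**Working it through.** The plan gives no dropout rate and no figure for this loss, so there is nothing of its own to reproduce. The size has to be shown under assumptions.

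**Inputs**
- Control fall rate: 1 per person-year (Sample size justification, where about one fall per person is expected).
- True rate ratio: 0.70 (assumed).
- Stopping hazard: 0.22 per year (assumed), so 1 − exp(−0.22) = 0.197 stop within the year.
- Frailty u: gamma with mean 1 and variance (dispersion) a = 1.5 or 4 (assumed).
- Risk-linked stopping: hazard 0.22 × (0.25 + 0.75u) (assumed).
- Every patient who stops counts as lost, with no telephone retrieval. This overstates the loss.

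**Falls discarded when stopping is unrelated to risk.** Falls accrue in proportion to observed time. Mean observed time is (1 − e^−0.22)/0.22 = 0.1975/0.22 = 0.8976 years per patient, of which completers supply 0.8025. Share lost = 1 − 0.8025/0.8976 = 0.106, about 11%.

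**Completers' fall rate when stopping is risk-linked.** The chance of completing is proportional to exp(−0.165u), since 0.22 × 0.75 = 0.165. Frailty among completers is again gamma, with mean 1/(1 + 0.165a). For a = 1.5 this is 1/1.2475 = 0.802. The completer rate ratio is then:
- link in controls only: 0.70/0.802 = 0.87
- link in intervention only: 0.70 × 0.802 = 0.56
- equal link in both arms: the factor cancels, 0.70

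For a = 4 the factor is 1/1.66 = 0.602, and the two one-arm ratios become 0.70/0.602 = 1.16 and 0.70 × 0.602 = 0.42. The size depends heavily on assumptions that the article cannot settle.

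**Simulation, 2,000,000 patients per arm.** The offset analysis is represented by falls divided by observed time.

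| Arms where stopping is linked to frailty | Dispersion | Recorded falls discarded | Completer ratio | Ratio per observed time |
|---|---|---|---|---|
| Neither | 1.5 | 11% | 0.70 | 0.70 |
| Both equally | 1.5 | 19% | 0.70 | 0.70 |
| Both equally | 4 | 29% | 0.70 | 0.70 |
| Controls only | 1.5 | not tabulated | 0.87 | 0.78 |
| Intervention only | 1.5 | not tabulated | 0.56 | 0.63 |

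**At trial size, with the negative binomial model fitted.** Assumptions: 191 per arm (382/2), 1 fall per year, dispersion 1, no clustering, 600 runs per row. Stopping percentages are nominal.

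| Stopping | True ratio | Complete cases: ratio, rejections | All patients with offset: ratio, rejections |
|---|---|---|---|
| 15%, unrelated to risk | 1 | 1.01, 6.3% | 1.01, 5.7% |
| 15%, unrelated to risk | 0.65 | 0.64, 73.5% | 0.64, 77.0% |
| 15%, linked in intervention arm only | 1 | 0.86, 16.5% | 0.94, 7.5% |
| 20%, linked in intervention arm only | 1 | 0.81, 25.8% | 0.92, 9.5% |
| 10% control, 25% intervention, linked in both | 1 | 0.86, 16.0% | 0.95, 7.2% |

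The first row is the benchmark for the rejection rates. In the first two rows, complete cases keep about 325 of 382 patients and discard about 8% of recorded falls. The last row shows that one and the same link to risk is enough for bias when the arms stop at different rates.

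**The case against.** The strongest objection is the telephone follow-up. A reader might infer that anyone who stops the diary is dropped with every month already returned. The document does not support that. Those patients are called and asked how many falls they had, which is the primary outcome, so a patient who answers can still have a complete count. The exclusion falls mainly on deaths, withdrawals and people who cannot be reached, and may be small. The article also does not define complete information, and nowhere says that twelve diary months are required.

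The SAP objection succeeds in part. The absence of an offset from a condensed article is no fault in itself, and imputation and sensitivity analyses may well be handled properly in the SAP. It does not reach the analysis set, which the article states.

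The label objection also succeeds in part. The article attaches intention to treat to compliance within the set and does not claim that every enrolled patient is analysed. The wording is misleading without being a false claim.

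On magnitude, the biased results come from deliberately unequal stopping, and a link in one arm only is an extreme case that nothing in the article supports. With an equal link at equal rates, the completer ratio is unbiased. The remedy is partial too: 0.78 and 0.63 are still not 0.70. All of this stands. It limits what can be said about bias and leaves the loss of information and the set definition untouched.

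**Conclusion.** The point holds as a badly fixed analysis set. Patients whose 12-month count stays incomplete after telephone retrieval are excluded together with recorded falls and follow-up time that the chosen model could use.

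The certain cost is information. At an assumed loss of about 20% with no retrieval, 11% of recorded falls are discarded if stopping is unrelated to risk, and 19% to 29% if it is frailty-related. At 15% unrelated stopping, power for a ratio of 0.65 is 73.5% against 77.0%.

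A reader might go further and conclude that the primary result will be biased. The document does not support this. Bias needs risk-related stopping that differs between arms, it can run in either direction, and the article gives neither a dropout rate nor a reason to expect a particular pattern. Its size is unknown. The set should be corrected before analysis, but the point does not by itself invalidate the planned comparison.

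**What to change.** Replace the definition of the set with wording such as: *The full-analysis set comprises all enrolled patients of randomised practices with any fall follow-up in months 0 to 12, analysed in the arm of their practice regardless of adherence. The negative binomial model includes the log of observed time in months 0 to 12, counting time covered by telephone information, as an offset.* Keep the analysis of patients with complete 12-month information as a sensitivity analysis.

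The cost is a few sentences in the protocol or SAP. Diary months are already dated; telephone calls need a note of the period that they cover.

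There are two limits. The offset assumes a constant fall rate over follow-up, which is not assured when the programme runs only for the first 16 weeks. It also reduces, but does not remove, bias from stopping tied to unmeasured fall risk. The sensitivity analyses already promised for the SAP are the place to examine both.

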**Methods/Design:**

PreFalls is a controlled multicenter prospective study with cluster-randomized allocation of about 40 general practices to an experimental or a control group. We aim to include 382 community dwelling persons aged 65 and older with an increased risk of falling. All participating general practitioners are trained to systematically assess the risk of falls using a set of validated tests. Patients from intervention practices are invited to participate in a 16-weeks exercise program with focus on fall prevention delivered by specifically trained local physiotherapists. Patients from practices allocated to the control group receive usual care. Main outcome measure is the number of falls per individual in the first 12 months (analysis by negative binomial regression). Secondary outcomes include falls in the second year, the proportion of participants falling in the first and the second year, falls associated with injury, risk of falls, fear of falling, physical activity and quality of life.

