## Methods/Design

### Study design and randomization

PreFalls is a controlled multicenter prospective study with cluster random allocation of participating general practices to an experimental or a control group. The study is performed in two regions (greater Munich and Nuremberg areas) in Bavaria, southern Germany. Two randomisation lists are computer generated by a statistician otherwise not involved in the study. The lists are stored by the two regional study coordinators. After the definitive inclusion of a general practice into the study, the coordinator of the respective region calls the coordinator of the other region who, after registering the practice, hands out the allocation information.

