### Intervention

Physicians taking part in the study are asked to name a certified local physiotherapist or an university trained sport scientist interested to act as exercise instructor (trainer) for the fall prevention program. If the general practitioner cannot name a trainer the coordination team will identify a qualified person. If the practice is randomised to intervention program the study centre invites the trainer to a special course lasting 8 hours. The course covers the standardised evaluated intervention program [39-41] as well as other study-related issues such as definition of falls and assessment procedures to enable trainers to answer upcoming questions of the participants.

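### The confirmatory model names the physiotherapist, not the randomised general practice, as its cluster, so the two-sided 5% test may be miscalibrated

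*Protocol article*

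**What the plan says.** Three parts of the protocol article bear on the cluster.

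- **Randomisation.** The section on study design and randomization describes "cluster random allocation of participating general practices to an experimental or a control group". The abstract puts the number of practices at about 40.
- **Sample size.** The justification assumes an intracluster correlation of 0.02, states that "a cluster size of 10 was considered to be realistic", and arrives at about 40 clusters and 382 individuals. The cluster count equals the practice count, so the cluster used for sizing is the practice.
- **Primary analysis.** The Statistics section chooses negative binomial regression at a two-sided 5% level and says that this approach "allows for further consideration of random effects as cluster (responsible physiotherapist) and region". No practice effect is mentioned.

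Two further statements show who has a trainer. According to the abstract, "Patients from practices allocated to the control group receive usual care". The Intervention section says "Physicians taking part in the study are asked to name a certified local physiotherapist or an university trained sport scientist", with the coordination team finding someone if the physician cannot. Then: "If the practice is randomised to intervention program the study centre invites the trainer to a special course lasting 8 hours". Naming a trainer thus applies to every practice, while activating the trainer depends on allocation.

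**The concern.** In a cluster-randomised trial the comparison between arms varies with the randomised units. The primary model therefore has to carry those units in both arms for its standard error to be right. Here the article names a different unit. A physiotherapist is a source of correlation among the patients who train together, and that happens only in the intervention arm. Among control patients the correlation comes from sharing a practice.

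What a trainer label does in the model depends on facts that the article does not give: whether each practice has its own trainer, whether a trainer may be named by practices in both arms, and what label control patients receive. At stake is the error rate of the single confirmatory test.

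**Working it through.** **Inputs from the article:** intracluster correlation ρ = 0.02 and cluster size m = 10 (Sample size justification); 10 to 15 patients per practice (Participating patients); about 40 practices in a balanced allocation, taken as 20 per arm; two-sided 5%.

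**The plan's own figure.** For 33% versus 20%, 80% power and a pooled chi-square test:

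n per arm = [1.96·√(2·0.265·0.735) + 0.842·√(0.33·0.67 + 0.20·0.80)]² / 0.13² ≈ 180, so 360 in all.

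Multiplied by the design effect of 1.18 this is 424.8, or about 425, not 382. The article used simulation software, so the gap needs an explanation of its own, but it does not decide this point. The useful part is 382/40 = 9.55 patients per cluster, which confirms that the cluster used for sizing is the practice.

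**Design effect.** DE = 1 + (m − 1)ρ. For m = 10: 1 + 9·0.02 = 1.18. For m = 15: 1 + 14·0.02 = 1.28.

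**Clustering omitted in both arms.** The true variance is DE times the modelled one, so type I error = 2·[1 − Φ(1.96/√DE)].

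- m = 10: 1.96/1.086 = 1.804, giving 7.1%. The standard error is 1 − 1/√1.18 = 7.9% too small.
- m = 15: 1.96/1.131 = 1.732, giving 8.3%.

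**Clustering ignored in the control arm only.** The true variance is proportional to 2·DE and the modelled one to DE + 1, so the ratio is 2·DE/(DE + 1).

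- m = 10: 2.36/2.18 = 1.083, giving 6.0%.
- m = 15: 2.56/2.28 = 1.123, giving 6.4%.

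**Simulation under the null.** These runs used a Gaussian working model (not the negative binomial), 20 practices of 10 per arm, ρ = 0.02 and 20,000 runs. The Monte Carlo standard error near 5% is √(0.05·0.95/20,000), about 0.15 percentage points.

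| How the cluster label behaves | Type I error |
|---|---|
| Trainer label coincides with practice (same as modelling practice) | 4.9% |
| Trainer shared by two practices of the same arm | 4.8% |
| Trainer shared by one practice in each arm, analysed as a within-trainer comparison | 7.0% |
| No cluster term | 6.9% (7.1% by formula) |
| All controls in one no-trainer level, REML | about 2.9% |

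The last row is low because the model charges the control mean with one whole cluster variance, where the truth is that variance divided by 20 practices. At an assumed ρ of 0.05 it falls to about 2.1%.

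**Sensitivity to ρ (assumed values).** With no cluster term and m = 10, the formula gives 6.1% at ρ = 0.01, 10.4% at 0.05 and 15.5% at 0.10. With practice modelled in both arms, the simulated rate is 4.9% at 0.02, 0.05 and 0.10.

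**The case against.** The strongest reply has three parts.

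**Control practices may have a trainer label.** A reader might infer that control patients have no physiotherapist and that the cluster is undefined for them. The Intervention section does not support that: every participating physician is asked to name a trainer, so the phrase about the responsible physiotherapist may be standing in for the practice. This stands as a limit on the claim. It does not rescue the wording. A trainer who never treats the control patients is not what correlates them, and nothing in the article makes trainers one per practice or confines them to one arm.

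**The wording is permissive and an SAP is announced.** Saying that a model allows for random effects describes a capability. Whether the term is compulsory is ordinary SAP content, and its absence from a condensed article is no fault. That is accepted. The no-cluster figures are a bound on what could happen, not a description of the plan. What remains is that the article does define the cluster and defines it as something other than the randomised unit. The topics it hands to the SAP (further analyses, multiplicity, imputation, sensitivity analyses) do not expressly include that definition.

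**The error rate need not be inflated.** A reader might infer that the standard error is simply wrong, or always too small. The table shows otherwise: two labelings keep the rate near 5%, and one makes the test conservative. Larger figures, 7.1% to 11.2%, come from simulating counts, but they need a dispersion of 4 and a practice log-rate SD of 0.3 to 0.5. The article states neither, and that test already rejected in 5.6% to 6.0% of runs with no clustering present. They are not relied on here.

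**Conclusion.** The point holds as a mismatch between the randomised unit and the cluster named for the confirmatory model. That mismatch follows from the text alone. Its effect on the test is conditional on how trainer labels are assigned, and its direction is uncertain. At the plan's own ρ and cluster size, type I error ranges from about 2.9%, through about 5%, to about 7%. With 15 patients per practice it reaches 6.4% if control clustering is ignored and 8.3% if all clustering is omitted.

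These figures rest on normal approximations and a Gaussian working model. They also apply an intracluster correlation, assumed in a calculation about the proportion of fallers, to an analysis of fall counts. Severity: should-fix, with moderate confidence.

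**What to change.** Replace the parenthetical cluster definition in the Statistics section, or settle it in the SAP before the final analysis, with: *The confirmatory negative binomial model includes a random intercept for general practice, the unit of randomisation, in both arms.* If correlation within training groups is of interest, add a trainer effect for intervention patients only, as a sensitivity analysis.

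The cost is one sentence and possibly slightly wider confidence intervals. No new data are needed, because each practice is registered when its allocation is given out. Settling it in advance also prevents a choice of cluster guided by the results.
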